### Intervention description {11a}

The underlying model of the WSS Review is peer-to-peer support facilitated by partnering schools (intervention group schools will be partnered with one another). The intervention is delivered to SENDCos who are expected to oversee the Whole School SEND (WSS) Review within their own school and to develop and implement a SEND Development Plan, targeting areas for improvement. Partner SENDCos also engage in peer-to-peer review of each other’s SEND provision, and mutual support throughout the trial.

The WSS Review process aims to raise awareness and give SENDCos more status such that they can become agents of change. Their role should shift from one with a pastoral focus to one that drives change in both teaching and learning. School partnering is pragmatic, being primarily based on geographic proximity, although other considerations such as advice from the regional nasen co-ordinator will also contribute to decisions that are made.

The programme is structured around five key contacts between nasen and the school/SENDCos, which provide a clear framework for ongoing support for each school, alongside a community of practice:
SEND Reviewer training (in two parts, July 2021 and September 2021)First engagement day (October 2021)First support visit from WSS project director (October 2021–January 2022)Second engagement day (February–March 2022)Second support visit from WSS project director (March–June 2022)

The *SEND Reviewer training* is a 1-day face-to-face event for SENDCos, facilitated by WSS Project Directors (nasen) to outline the project vision and aims and to deliver SEND Reviewer and peer mentor training. SENDCos from partner schools will jointly attend a training session in their region and training will be delivered to a standardised plan.

Between the training and the first engagement day, partner schools will do a peer-to-peer review of each other’s SEND provision in accordance with a structured process. Doing so will enable them to identify strengths, areas for development and stakeholders who might be involved in initiatives to support SEND students.

The *first engagement day* will be held on a regional basis and will provide an opportunity for SENDCos to begin to write their school’s SEND Development Plan, specifying three areas for development, relevant actions for each area and key stakeholders to involve. The engagement day will also form the basis of a regional community of practice for sharing knowledge, ideas and experience. It will also provide opportunities for collaborating and developing local networks.

The draft Development Plan will be shared with senior leaders and governors at a Full Governing Body meeting before the *first support visit by a WSS Project Director.* The purpose of the visit will be to review the school’s SEND Development Plan with the SENDCo and a senior leader, as well as to meet the head teacher, provide one-to-one coaching and address the SENDCo-led agenda for the day. Following the first support visit, the SENDCo will work with senior leaders to implement the SEND Development Plan.

A *second engagement day* will provide tailored SEND development based on regional feedback from school visits, review the engagement of stakeholders and facilitate regional sharing of best practice. Following this event, SENDCos will continue to work with senior leaders to implement their schools’ SEND Development Plan.

Finally, a *second support visit by a WSS Project Director* will discuss the action plan implementation, reviewing progress and next steps for SEND provision, providing a one-to-one coaching session and collecting anecdotal evidence to support a final review report.

### Criteria for discontinuing or modifying allocated interventions {11b}

Less confident SENDCos (ascertained at the first engagement day) will be visited first to ensure that they are better placed to implement their plans straight away.

### Strategies to improve adherence to interventions {11c}

The project team has established a strong communications strategy that emphasises the importance of schools engaging with the intervention and stressing the benefits of their involvement. Should a school drop out of the intervention arm of the study prior to completing the peer review process then the remaining partnered school will join another pair to form a trio. Alternatively (and dependent on the stage of the process that has been reached at the time), a WSS Project Director will undertake the review. Should a school drop out of the intervention arm of the study after completing the peer review process, the remaining school will still receive peer support through the regional support network of schools and will be prioritised in the WSS team school visit schedule.

### Relevant concomitant care permitted or prohibited during the trial {11d}

We have not specified any concomitant care to be permitted or prohibited.

### Provisions for post-trial care {30}

Students will be told to tell their teacher if they feel any negative emotions as a result of completing the SDQ (see below) and staff will be made aware of the support required for students in these circumstances. Staff will be advised to look out for signs of distress if students do not talk directly to teachers. Identifying the support structures and services available in a school will be achieved through a school audit prior to the administration of the SDQ. This will ensure that any services and support offered currently in a participating school are clearly identified so that teachers will know who to notify (e.g. parents, other service organisations such as social services) and how to deal with such matters.

The developers (nasen) will oversee the delivery of the SEND Review Process and will take action if necessary to address staff feeling professionally vulnerable. Training and events for SENDCos will provide guidance on how to best manage change.

### Outcomes {12}

Table 1 gives an overview of the primary and secondary outcomes.

**Table 1 Tab1:** Primary and secondary outcomes

	Outcome	Source	Measure	Analyses
**Primary outcome**				
Attainment	Mark obtained in GSCE English language	Exam boards via schools	Continuous	Pupils with a SEND designation
				All pupils
**Secondary outcomes**				
Attainment	Mark obtained in GCSE mathematics	Exam boards via schools	Continuous	Pupils with a SEND designation
				All pupils
	Grade obtained in GCSE English language	Exam boards via schools	1–9; 0 (unclassified)	Pupils with a SEND designation
	Grade obtained in GCSE mathematics	Exam boards via schools	1–9; 0 (unclassified)	Pupils with a SEND designation
Attendance and exclusions	Unauthorised absences	Schools	Count of number of authorised absences in school year	Pupils with a SEND designation
	Authorised absences	Schools	‘1’ = unauthorised absence observed in the relevant school year, ‘0’ otherwise	Pupils with a SEND designation
	Exclusions	Schools	‘1’ = exclusion observed in the relevant school year, ‘0’ otherwise	Pupils with a SEND designation
Wellbeing	Difficulties	Pupil self-report	Total number of difficulties (max 20)	Pupils with a SEND designation
				All pupils

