##### Attendance and exclusions outcomes

The WSS Review aims to bring about a change in school culture, promoting an inclusive and supportive environment as well as addressing specifically the needs of children with SEND in the classroom. These needs can often go unmet leading to poor attendance and in some cases exclusion from school. The trial therefore includes three secondary attendance and exclusion outcomes.
Authorised absences: a count of the number of authorised absences in the relevant school year depending on the cohort being considered.Unauthorised absences: a binary dependent variable for each pupil coded to ‘1’ where an unauthorised absence is observed in the relevant school year, ‘0’ otherwise.Exclusions (temporary fixed term, permanent): a binary dependent variable for each pupil capturing whether exclusions from school were recorded in the relevant school years.

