##### Attendance and exclusions

Analysis of attendance and exclusions outcomes will be adjusted on the basis of baseline measures of attendance for the school year 2019/20 (noting the shortening of the school year due to the Covid-19 pandemic and the closure of schools). These measures relate to the period of time prior to randomisation, which will take place in June 2021. The covariate will be derived by summing the total number of absences (both authorised and unauthorised) for each pupil for the school year 2019/20.

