**Attendance and exclusion outcomes**					
**Number of authorised absences in previous school year 2022/2023**	Count negative binomial hierarchical	Yes	Yes	• Number of authorised absences in school year 2019/2020 • Month of birth • Sex	Year 9
**Number of authorised absences in previous school year 2023/2024**	Count negative binomial hierarchical	Yes	Yes	• Number of authorised absences in school year 2019/2020 • Month of birth • Sex	Year 8
**At least one unauthorised absence in school year 2022/2023**	Binary logistic hierarchical	Yes	Yes	• Number of absences in school year 2019/2020 • Month of birth • Sex	Year 9
**At least one unauthorised absence in school year 2023/2024**	Binary logistic hierarchical	Yes	Yes	• Number of absences in school year 2019/2020 • Month of birth • Sex	Year 8
**At least one exclusion from school in school year 2022/2023**	Binary logistic hierarchical	Yes	Yes	• Number of absences in school year 2019/2020 • Month of birth • Sex	Year 9
**At least one exclusion from school in school year 2023/2024**	Binary logistic hierarchical	Yes	Yes	• Number of absences in school year 2019/2020 • Month of birth • Sex	Year 8

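### Table 1 interchanges the labels for authorised and unauthorised absence, the absence baseline is defined in two ways, and unauthorised absence is analysed only as any/none without a stated reason

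*Protocol article*

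**What the plan says.** The protocol article defines the absence outcomes in three places and their baseline in two.

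- **Table 1.** The row labelled unauthorised absences has the measure "Count of number of authorised absences in school year". The row labelled authorised absences is coded 1 for "unauthorised absence observed in the relevant school year, ‘0’ otherwise".
- **Attendance and exclusions outcomes (text).** "Authorised absences: a count of the number of authorised absences in the relevant school year". Unauthorised absence is "a binary dependent variable for each pupil coded to ‘1’ where an unauthorised absence is observed in the relevant school year".
- **Table 4 (SEND-only models).** Authorised absences are modelled as a hierarchical negative binomial count. The unauthorised outcome for the year 9 cohort is "At least one unauthorised absence in school year 2022/2023", with a hierarchical logistic model; the year 8 cohort has the same form a year later.
- **Baseline measures, Attendance and exclusions.** "The covariate will be derived by summing the total number of absences (both authorised and unauthorised) for each pupil for the school year 2019/20".
- **Table 4, covariate column.** The authorised outcome is adjusted for "Number of authorised absences in school year 2019/2020". The unauthorised and exclusion outcomes are adjusted for the number of absences in that year, with no type given.

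The opening of Baseline measures sets a general rule: where possible, each outcome is adjusted for a pre-randomisation measure of the same outcome.

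**The concern.** The table that introduces the outcomes contradicts the text and the model table on which type of absence is the count and which is the flag. Someone reading by row label would report each result under the wrong name.

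The baseline is unsettled in the same way. Whoever codes the adjusted models must choose between one summed covariate for every attendance outcome and a covariate that differs by outcome.

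The third matter is a choice rather than a contradiction. Reducing absences is a listed objective, and the theory of change expects absenteeism to fall. With any/none, a pupil who goes from fifty unauthorised absences to one scores 1 both times. Authorised absence keeps its full count, and the article does not say why the two are treated differently. A real reduction in unauthorised absence could go largely unseen.

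**Working it through.** **1. Outcome definitions side by side**

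| Place | Authorised absence | Unauthorised absence |
|---|---|---|
| Table 1, by row label | 0/1 flag (of unauthorised absence) | count (of authorised absences) |
| Outcome text | count | any/none |
| Table 4 | count, negative binomial | any/none, logistic |

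The text and Table 4 agree, and each Table 1 measure is complete and sensible in itself. The two row names have simply been exchanged. Correcting them changes no number in the plan.

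**2. Baseline covariate side by side**

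| Outcome | Baseline section | Table 4 |
|---|---|---|
| Authorised count | sum of both types, 2019/20 | authorised only, 2019/20 |
| Unauthorised any/none | sum of both types, 2019/20 | number of absences, 2019/20 |
| Any exclusion | sum of both types, 2019/20 | number of absences, 2019/20 |

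The first row is a direct conflict. The other two are compatible only if the unspecified number of absences means the sum. A sum is not a measure of the same outcome as unauthorised absence, so it does not meet the general rule where a like-for-like measure can be had. One appears available: the summed covariate is built from both types, and Model 3 of the primary analysis lists unauthorised absences before randomisation as a covariate in its own right.

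**3. Information kept by any/none**

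The article gives no power figure, mean or dispersion for absence, so there is no stated figure to reproduce. Everything below is an assumption shown over a range.

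Let a pupil's yearly count be negative binomial with mean m and size k, so that the variance is m + m²/k. For the log of the mean, with k known:

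- information in the count: I_count = km/(k + m)
- probability of no absence: P0 = (k/(k + m))^k
- information in any/none: I_any = I_count² × P0/(1 − P0)
- share kept: I_any/I_count = I_count × P0/(1 − P0)

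Example, m = 2 and k = 1: I_count = 2/3, P0 = 1/3, share = (2/3) × (1/3)/(2/3) = 0.33.

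Example, m = 20 and k = 0.2: I_count = 4/20.2 = 0.198, P0 = (0.2/20.2)^0.2 = 0.397, share = 0.198 × 0.397/0.603 = 0.13.

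| Mean m | Share kept, k = 0.2 | Share kept, k = 1 |
|---|---|---|
| 0.1 | 0.79 | 0.91 |
| 0.5 | 0.50 | 0.67 |
| 1 | 0.39 | 0.50 |
| 2 | 0.30 | 0.33 |
| 5 | 0.21 | 0.17 |
| 10 | 0.16 | 0.09 |
| 20 | 0.13 | 0.05 |

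**4. Dilution by school-level variance**

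The shares above are at pupil level. With 25 SEND pupils per school and cohort (Sample size section) and a school-level variance v of the log mean, the trial-level share is roughly (v + 1/(25 I_count))/(v + 1/(25 I_any)). The value of v is not in the documents.

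For m = 2 and k = 1, the two pupil terms are 1/(25 × 0.667) = 0.06 and 1/(25 × 0.222) = 0.18. The share is then 0.06/0.18 = 0.33 at v = 0, 0.12/0.24 = 0.50 at v = 0.06, and 0.24/0.36 = 0.67 at v = 0.18. For m = 20 and k = 1, the terms are 0.042 and 0.882, and the same values of v give 0.05, 0.11 and 0.21.

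**The case against.** Four stronger readings are tempting, and the documents do not support them.

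- **That following Table 1 would produce the wrong variables.** Each measure cell names its own quantity, so coding from that column gives the intended variables. Only the names beside them are wrong, and the article introduces the table as an overview. This objection stands: the swap is a labelling error that the text and Table 4 resolve.
- **That unauthorised absence is a key target of the programme.** The objectives refer to absences and exclusions, the outcome text to poor attendance, and the theory of change to absenteeism. None singles out unauthorised absence, and absence is a secondary objective.
- **That the outcome-year count is certainly held.** For the outcome year, the Outcome data section says only that absence data will be obtained, without giving their form. A count is a fair inference, because a count of authorised absences is planned from the same extract, but it is an inference.
- **That any/none discards most of the information.** This is true for means of about 2 and above, but not where unauthorised absence is rare. No distribution is given.

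It can also be said that any/none is prespecified consistently, has a matching model, is easy to interpret, and may be justified in the full online protocol, which is not shown. That is fair, and it makes the third part a matter of judgement. It does not alter the fact that the outcome cannot register a reduction short of zero. On the baseline, it can be argued that aligning the wording is enough for a covariate in secondary analyses. Some alignment is needed in any case, and the plan's own same-outcome rule points to like-for-like measures.

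**Conclusion.** The point holds in three parts of unequal strength.

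1. The interchange of labels in Table 1 is certain and editorial.
2. The conflict over the baseline covariate is certain. It affects adjustment in the secondary attendance models.
3. The any/none form for unauthorised absence is a weak choice for an objective framed as reducing absences, and the article gives no reason for treating the two types differently.

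The size of the third part depends on assumptions. With negative binomial counts and size 0.2 to 1, any/none keeps about 30–33% of the pupil-level information at mean 2 and 5–13% at mean 20, but 50–67% at mean 0.5 and more below that. School-level variance dilutes the loss in the trial estimate by an amount the documents do not allow one to fix. The primary outcome is untouched.

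**What to change.** - Exchange the two row labels in Table 1.
- Use like-for-like 2019/20 baselines: authorised absences for the authorised outcome, unauthorised absences for the unauthorised outcome. Bring the baseline section and Table 4 into agreement, and state in Table 4 which type of absence each covariate counts, including in the exclusion rows.
- Analyse unauthorised absence also as a count, in the hierarchical negative binomial model already planned for authorised absence, and report an incidence rate ratio beside the any/none result. First confirm that the outcome-year extract holds the count. If any/none is to remain the only analysis, state why.

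The cost is a few wording changes and one further model of a kind already in the plan, settled before the outcome data are analysed. No new data collection is needed if the extract holds the count. The downside is that the count is skewed, so the fit of the negative binomial model must be checked.

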#### Primary outcome

The primary outcome is attainment in GCSE English language for pupils designated SEND; that is with SEND support or with an Education, Health and Care Plan (ECHP) on Tuesday 1st September 2020. The outcome metric will be standardised (equated) marks in GCSE English Language, obtained via schools from exam boards.

English language was chosen as the primary outcome measure because command of written and spoken language is important in accessing learning in general, and is a determinant of future advancement. Reliance on national examinations for assessment is partly a practical decision but also one that reflects substantive concerns. Importantly, examination scripts are marked ‘blind’ to the pupil’s status with regard to this trial. From a practical perspective, adopting attainment at GCSE as the primary outcome has a number of further advantages. First, considerable resources are devoted by exam boards to the writing and validation of GCSE questions; therefore, examination marks might be considered reliable and valid measures of attainment in and of themselves. Second, the costs of collecting pupil level GCSE results are low compared to the costs of the alternative, which is administering commercial standardised assessment tests. Third, unlike administering separate standardised assessments of literacy and language, using GCSE marks as the primary outcome imposes no additional data collection burden on schools. Fourth, as a measure, it is also less affected by the loss to follow-up than the alternatives.

#### Secondary outcomes

Secondary outcomes are grouped into three categories: (a) further attainment outcomes, (b) attendance and exclusions outcomes and (c) wellbeing outcomes.

##### Further attainment outcomes

The underlying intervention theory provides an account of how the WSS Review is expected to raise general attainment, specifically for SEND pupils but also among the wider student body. As a result, the selection of secondary outcomes is informed by the expectation that aspects of attainment other than English language will improve as a consequence of the WSS Review. Given the importance of attainment in mathematics for future advancement, marks at GCSE mathematics is a secondary outcome for SEND-designated and all pupils respectively.

Whilst our primary outcome focus is on marks (given these might be considered sensitive to small changes in attainment and provide a continuous attainment score), GCSE grades are also of interest and are therefore also included as secondary outcome measures. Grades are well understood—results showing an intervention has an effect on average GCSE grade can be clearly interpreted by stakeholders. Moreover, closing the attainment gap is a central concern and it is a grade that ultimately reflects this and can determine future life prospects (e.g. the opportunity to undertake further study and apply for jobs which specify particular grades as entry requirements).

Grades obtained in both English and mathematics will be on a 1–9 scale with unclassified grades coded to ‘0’.

##### Attendance and exclusions outcomes

The WSS Review aims to bring about a change in school culture, promoting an inclusive and supportive environment as well as addressing specifically the needs of children with SEND in the classroom. These needs can often go unmet leading to poor attendance and in some cases exclusion from school. The trial therefore includes three secondary attendance and exclusion outcomes.
Authorised absences: a count of the number of authorised absences in the relevant school year depending on the cohort being considered.Unauthorised absences: a binary dependent variable for each pupil coded to ‘1’ where an unauthorised absence is observed in the relevant school year, ‘0’ otherwise.Exclusions (temporary fixed term, permanent): a binary dependent variable for each pupil capturing whether exclusions from school were recorded in the relevant school years.

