### Objectives {7}

The primary objective of this trial is to test the efficacy of the WSS Review at *raising attainment in English Language at General Certificate of Standard Education (GCSE)* among pupils designated SEND. Other objectives are to test the efficacy of the WSS Review (for pupils both with and without a SEND designation) at:
Raising attainment in GCSE mathematicsReducing absences and exclusions from schoolImproving pupils’ wellbeing

The trial is therefore designed to test the WSS Review theory of change (see the ‘Discussion’ section), which assumes the widespread effects of the intervention towards transformational change both for pupils with and without a SEND designation. It is expected that this to occur through fostering and promoting a more inclusive and supportive school culture and that the intervention will have a direct effect on the classroom through encouraging SENDCos to engage more fully with both teaching practice and the learning environment. We therefore also expect a consequent improvement in pupils’ attainment, particularly among pupils designated SEND. The WSS Review is hypothesised to enhance the inclusivity and supportiveness of the school, and as such is anticipated to reduce absences and exclusions particularly among pupils designated SEND. It is also expected that the Review will improve pupils’ wellbeing through similar mechanisms.

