## Assignment of interventions: Blinding

### Who will be blinded {17a}

There are no specific measures for blinding. However, whilst the group assignments will be known to the researchers, data collectors, developers, SENDCos and other school staff, it is unlikely that pupils will be aware of the implementation of the intervention as distinct from other school activities.

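### The objective is to reduce absences, but no outcome measures total absence: an authorised count and an any/none unauthorised indicator cannot be combined into a net change

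*Protocol article*

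**What the plan says.** Objectives {7} name absences and exclusions together, without splitting absence by authorisation. The hypothesis is that the Review "is anticipated to reduce absences and exclusions particularly among pupils designated SEND".

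The section on attendance and exclusions outcomes gives what reads as a closed list: "The trial therefore includes three secondary attendance and exclusion outcomes". The first is "Authorised absences: a count of the number of authorised absences in the relevant school year depending on the cohort being considered". The second is binary, coded 1 "where an unauthorised absence is observed in the relevant school year". The third is a binary indicator of exclusion.

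Table 4 follows that list for the SEND-only samples. Authorised absences get the model "Count negative binomial hierarchical". Unauthorised absence is modelled by hierarchical logistic regression on, for the year 9 cohort, "At least one unauthorised absence in school year 2022/2023". The Secondary analysis section reports binary outcomes as relative risks and counts as incidence rate ratios. No table models total absence as an outcome.

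A total does appear at baseline. Under Baseline measures, for 2019/20, "The covariate will be derived by summing the total number of absences (both authorised and unauthorised) for each pupil".

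Table 1 gives schools as the source of the absence data. Section {17a} states that "the group assignments will be known to the researchers, data collectors, developers, SENDCos and other school staff".

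**The concern.** The objective concerns how much school pupils miss. Neither outcome answers that. The count leaves out unauthorised sessions, and the indicator ignores how many unauthorised sessions there were once a pupil has had one.

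This has two consequences. First, a real reduction in unauthorised sessions among pupils who still have at least one changes neither outcome. Second, if sessions move from one class to the other, the two estimates move without any change in attendance, and the reader cannot net one against the other. Absence data come from schools whose staff know the allocation, so the second possibility cannot be ruled out, although nothing in the article shows that it would happen.

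At stake is the conclusion on one stated objective: a gain could be missed, or a mixed result reported when attendance is unchanged.

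**Working it through.** The article gives no absence rates and no power figure for the attendance outcomes, so there is no figure of its own to reproduce. The check is a reading of the definitions plus two illustrations with assumed rates.

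**Step 1: definitions side by side**

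| Item | Authorised absence | Unauthorised absence | Total absence |
|---|---|---|---|
| Outcome section | count | any/none | not defined |
| Table 4 model | negative binomial | logistic | none |
| Effect measure | incidence rate ratio | relative risk | none |
| Baseline section, 2019/20 | part of total | part of total | derived as covariate |

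Write A for a pupil's authorised count and U for the unauthorised count. The trial estimates contrasts in E(A) and in P(U ≥ 1). The objective needs a contrast in E(A + U) = E(A) + E(U). E(U) is not determined by P(U ≥ 1), so the net change cannot be obtained from the two planned estimates.

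**Step 2: a shift between classes with attendance unchanged**

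Assume mean A = 10, mean U = m, and that a random 25% of unauthorised absences become authorised.

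- Authorised rate ratio = (10 + 0.25m)/10.
- Mean U after the shift = 0.75m.
- Poisson: P(U ≥ 1) = 1 − exp(−mean).
- Negative binomial with k = 0.4: P(U ≥ 1) = 1 − (1 + mean/0.4)^(−0.4). Random removal of sessions leaves k unchanged.

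For m = 4, one absence moves (0.25 × 4):

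- Authorised: 11/10 = 1.10.
- Any unauthorised, Poisson: 0.950/0.982 = 0.97.
- Any unauthorised, negative binomial: 0.575/0.617 = 0.93.
- Total: 14 before and 14 after.

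Over a range of m:

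| m | Authorised rate ratio | Relative risk, Poisson | Relative risk, negative binomial | Total before and after |
|---|---|---|---|---|
| 2 | 1.05 | 0.777/0.865 = 0.90 | 0.464/0.512 = 0.91 | 12 |
| 4 | 1.10 | 0.950/0.982 = 0.97 | 0.575/0.617 = 0.93 | 14 |
| 8 | 1.20 | 0.9975/0.9997 = 1.00 | 0.670/0.704 = 0.95 | 18 |

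**Step 3: a real fall that neither outcome sees**

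Simulation of 1,000,000 pupils, both counts negative binomial: authorised mean 14 (k = 1.0); unauthorised mean 2, 4 or 8 (k = 0.3, 0.4, 0.6). Each pupil with more than one unauthorised absence has the number halved, rounded up, so nobody reaches zero.

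| Unauthorised mean | Mean authorised, before and after | P(U ≥ 1), before and after | Total before | Total after | Fall in total |
|---|---|---|---|---|---|
| 2 | 13.97 | 0.458 | 15.97 | 15.11 | 0.86/15.97 = 5% |
| 4 | 14.02 | 0.618 | 18.02 | 16.20 | 1.82/18.02 = 10% |
| 8 | 13.98 | 0.797 | 21.99 | 18.20 | 3.79/21.99 = 17% |

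Both planned outcomes are unchanged while total absence falls. This needs no assumption about recoding.

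**Step 4: consistency of the passages to be edited**

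- Table 1 gives the unauthorised row a count of authorised absences, and the authorised row the any/none indicator of unauthorised absence. The outcome section and Table 4 have them the other way round.
- The baseline section sums both classes for the attendance and exclusion analyses. Table 4 adjusts the count model for authorised absences alone, and the two binary models for the number of absences.

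**The case against.** The strongest reply concerns the mechanism. A reader might infer that unblinded schools in the intervention arm will relabel absences, so that the planned outcomes could not be told apart from better attendance. The article does not support this. It describes training, peer review, development plans and support visits, and does not mention attendance coding. It does not say that SENDCos decide authorisation. Knowledge of allocation makes differential recording possible, not documented.

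Nor would every shift be hidden. In Step 2 the authorised count rises while the unauthorised indicator falls or barely moves. Opposed movement would be a partial warning, since better attendance would not raise the authorised count. An exact match between a real fall and relabelling can be constructed (authorised mean 12.62 and P(U ≥ 1) 0.618 in both, with totals of 16.62 and 18.02). It needs authorised sessions to become unauthorised, and only among pupils who already have an unauthorised absence. What survives is that the size of the net change cannot be recovered.

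A reader might also take the 25% fall in mean unauthorised absences as an apparent 25% benefit. The trial does not estimate that ratio. On its any/none outcome the same shift gives about 0.93 to 0.97 at a mean of 4.

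Finally, reporting two classes of absence is a legitimate choice, the outcomes are secondary, and a total could be reported descriptively from the same data. All of that stands. It does not supply a planned estimate for an objective stated as reducing absences, and the outcome list reads as complete.

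**Conclusion.** The point holds in a limited form. The objective is fewer absences, and the planned outcomes yield no estimate of net change in absence. That follows from the definitions alone. A fall in unauthorised absence that leaves every affected pupil with at least one is invisible; in the simulation it amounted to 5% to 17% of total absence. A shift between classes, if it occurred, could not be netted out. With assumed means of 10 and 4 and a 25% shift, the authorised rate ratio is 1.10 and the relative risk about 0.93 to 0.97, with the total unchanged at 14.

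All sizes rest on assumed means, dispersions and shift fractions, because the article gives no absence rates. The documents do not support a claim that schools would recode absences or that the attendance results would be biased. The primary analysis and the sample size calculation are unaffected. This is a worthwhile, inexpensive improvement to a secondary outcome.

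**What to change.** Add total absences (authorised plus unauthorised) in the relevant school year as a secondary attendance outcome in Table 1, in the section on attendance and exclusions outcomes, and in Table 4. Use the negative binomial hierarchical model already planned for the authorised count, with the 2019/20 total from the baseline section as covariate. Keep the authorised and unauthorised outcomes as components that show the mix. The total need not be made the lead attendance outcome.

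In the same edit:

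- Correct the two swapped absence measures in Table 1 so that they agree with the outcome section and Table 4.
- Reconcile the baseline covariate: the baseline section specifies the total, while Table 4 uses authorised absences only for the count model.

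Section {18a} already provides for extracting absence data for the outcome years, so no new data source is needed. The cost is one more secondary outcome and one more model per cohort.
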